#### 9.3.2. Primary endpoint(s) analysis

The immune response measured by immunoassay 14 days after randomisation between the two arms will be tested by one-tailed t-test assuming symmetric distribution of lognormal transformation. Geometric means will be calculated as the mean of the assay results after making the logarithm transformation and then exponentiating the mean to express results on the original scale. One-sided 95% CIs will be obtained by taking natural log transforms of concentrations/titers, calculating the 95% CI with reference to the t-distribution, and then exponentiating the confidence limits. In other case, Mann-Whitney-Wilcoxon test will be used.

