- Immune response measured by NAV at 28 days after the randomization ( $\pm 2$  days)
- Correlation of immune response measured by NAV and immunoassay (antibodies against SARS-CoV-2 spike protein).
- Change in immune response from baseline (randomization visit) to 14 and 28 days after COMIRNATY vaccination in the immediate and control groups.
- Differences in immune response at the different time points by both immunoassay (antibodies against SARS-CoV-2 spike protein) and NAV tests.
- Percentage of patients reaching a FRNT50 GMTs  $>1000$  at 14 and 28 days (or the figure having best evidence in the literature at the time of analysis)
- Maintaining a FRNT50 GMTs  $>1000$  (or the figure having best evidence in the literature at the time of analysis) at 3, 6 and 12 months.

A full description of statistical analysis will be made in the SAP.

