#### **Randomisation and blinding:**

- Randomization will be centralized, and each participant will be randomized stratified by age and centre. Randomization will be in a proportion of 2:1 (COMIRNATY:No vaccination)
- This is an open-label trial.

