### **6.3. Measures to Minimize Bias: Randomization**

This is an open-label clinical trial.

The randomization list will be generated using software SAS 9 for Windows. The randomization list will be imported into the REDCap program so the researchers can randomize candidate subjects using an easier-to-use interface. Subjects that meet the selection criteria will be randomized in a 2:1 ratio between the two treatment groups (Intervention arm: administration of a COMINARTY boosted dose vs Control arm: no administration of boosted dose), stratifying by center, gender and age (18-49 years, 50-59 years and  $\geq 60$  years), in order to achieve balanced randomization in the two treatment groups. The assignment of treatment to each subject will be centralized, keeping the sequence hidden.

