### **Visit 1. Randomization**

- PCR
- Review medical history
- Review medication history
- Measure vital signs (body temperature, pulse, blood pressure).
- Blood extraction for immune response evaluation.
- Blood extraction for lab safety determinations.
- Randomization.
- Pregnancy test

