### 9.3. Statistical Analyses

#### 9.3.1. General considerations

All analyses will be carried out using the statistical software SAS, version 9.4 of the SAS system for Windows.

All continuous variables will be summarized using the following descriptive statistics: n (non-missing sample size), mean, standard deviation (SD), 1st quartile, median, 3rd quartile, maximum and minimum. Absolute and relative frequencies (based on the non-missing sample size) of observed levels will be reported for all categorical variables.

All continuous variables will be tested for normality hypothesis assumption with the kolmogorov-Smirnov test. The antibodies binding to the SARS-CoV-2 S protein will be measured as lognormal distribution to obtain more nearly symmetric distribution.

The number of participants and the flowchart of the study will be presented. The period of enrolment and the total number of participants screened to be included in the study will be presented. The number of ineligible participants and the total number of randomized participants will be presented. The number of participants who never receive the study intervention will also be presented by treatment group and those who were included in the full analysis set and the safety analysis set will be presented.

Baseline is considered as the day 1 visit and the baseline data is data collected just before intervention at day 1. Participants with missing baseline value will be excluded from the analysis.

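### The primary t-test leaves out the baseline titre and the randomisation strata, and its Mann-Whitney fallback names no estimate of the ratio being tested

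*Protocol*

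**What the plan says.** - **Primary test (Protocol 9.3.2).** "The immune response measured by immunoassay 14 days after randomisation between the two arms will be tested by one-tailed t-test", on the log scale, with geometric means and one-sided limits. No covariate or stratum is named. If the distributional assumption fails: "In other case, Mann-Whitney-Wilcoxon test will be used". Section 9.3.3 repeats this scheme for the secondary immunogenicity endpoints.
- **Normality check (9.3.1).** "All continuous variables will be tested for normality hypothesis assumption with the kolmogorov-Smirnov test". No significance level is given, and nothing says whether the arms are tested separately or pooled.
- **Hypothesis (9.1).** A ratio, G(Y1)/G(Y2), equal to 1 against greater than 1.
- **Baseline titre.** Visit 1 in section 8 lists "Blood extraction for immune response evaluation". Section 9.3.1 adds: "Participants with missing baseline value will be excluded from the analysis". The only planned use of baseline is among the other comparisons in the synopsis: "Change in immune response from baseline (randomization visit) to 14 and 28 days after COMIRNATY vaccination".
- **Strata.** Section 6.3 has randomisation "stratifying by center, gender and age", with three age groups. The randomisation paragraph of 4.1 says "each participant will be randomized stratified by age and centre", without sex, although the design paragraph of 4.1 lists site, sex and age. Section 1.1 has the same split: its trial overview includes sex and its randomisation entry does not.

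**The concern.** A covariate that predicts the outcome is measured before dosing in everyone who can enter the analysis, and the primary test sets it aside. A participant can even be dropped for lacking a value the test never uses. Infection before the first vaccine dose is not an exclusion (5.2 excludes only documented COVID-19 since that dose), so baseline titres may be spread out, although the protocol gives no figure. Where the strata predict titre, ignoring them after stratified randomisation also makes the standard error too large.

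The second issue is what gets reported. The Day 14 result decides whether the hypothesis is taken as confirmed, which in turn bears on whether controls are considered for a dose at Day 28 (1.1, 4.1, 6.1.2). The primary test should therefore be known before the data are. Here it hangs on a check with no stated level. Mann-Whitney does not address a ratio of geometric means unless a pure shift on the log scale is assumed, and no estimator is named to go with it.

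**Working it through.** **Inputs (Protocol 9.5).** Ratio 1.35, so the log difference is ln 1.35 = 0.3001. Coefficient of variation (CV) 1.2, so the log SD is sqrt(ln(1 + 1.2²)) = sqrt(ln 2.44) = 0.9445. Allocation 400/200, alpha 0.01 stated as one-sided, power 80%, 15% non-evaluable (400 × 0.85 = 340; 200 × 0.85 = 170).

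**The plan's own figure.** Control n = 1.5 × [SD × (z_alpha + z_0.80) / ln ratio]².
- With z_alpha = 2.576 (two-sided 0.01): 1.5 × (0.9445 × 3.417 / 0.3001)² = 173.5, the table's 173.506. All 12 rows reproduce this way.
- With z_alpha = 2.326 (one-sided 0.01, as the text states): 149.1. This mismatch is a separate matter. Power is shown below on the stated one-sided basis first.

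**Effect of adjusting for baseline.** If rho is the correlation between baseline and Day 14 log titre, the residual SD is SD × sqrt(1 − rho²). The protocol gives no rho, so 0.3 to 0.7 is an assumed range. Power = Φ(0.3001 / SE − z_alpha).
- 340/170, unadjusted: SE = 0.9445 × sqrt(1/340 + 1/170) = 0.0887; 0.3001/0.0887 = 3.383; Φ(3.383 − 2.326) = 85.5%.
- 340/170, rho 0.5: 3.383 / sqrt(0.75) = 3.906; Φ(1.580) = 94.3%.

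| rho | Variance reduction | Power 340/170, one-sided 0.01 | Power 400/200, one-sided 0.01 | Power 347/173.5, two-sided 0.01 |
|---|---|---|---|---|
| 0 (as planned) | 0% | 85.5% | 91.0% | 80.0% |
| 0.3 | 9% | 88.9% | 93.6% | 84.3% |
| 0.5 | 25% | 94.3% | 97.2% | 91.5% |
| 0.7 | 49% | 99.2% | 99.8% | 98.6% |

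Strata alone add less: if they explain an assumed 2% to 10% of the variance, power at 400/200 moves from 91.0% to between 91.6% and 93.8%.

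**Effect of the fallback.** Simulation at one-sided 0.01, 400/200, ratio 1.35 for power, with the normality test run in each arm at an assumed 5% level:

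| Log titres | Switch occurs | Power, t-test | Power, Mann-Whitney | Power, two-stage | Type I error, two-stage |
|---|---|---|---|---|---|
| Normal | 9% | 91.1% | 89.7% | 91.0% | 0.011 |
| Heavy-tailed (t, 5 df) | 92% | 91.0% | 95.9% | 95.8% | 0.0125 |
| Skewed | 100% | 90.5% | 94.9% | 94.9% | 0.008 |

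If the arms were instead pooled for the normality test, it would reject in 4% of trials at a ratio of 1.35, 9% at 3 and over 99% at 10. At a ratio of 10 with 340/170 the effect is ln 10 / 0.0887 = 26 standard errors, so either test would detect it and only the reported quantity could change.

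**The case against.** The strongest reply is that a two-sample t-test in a randomised trial is valid, that ignoring strata errs on the conservative side, and that the planned 80% power is reached without adjustment at the stated one-sided 0.01. Every gain in the first table rests on a correlation the protocol does not give. On this view, covariate adjustment is an efficiency preference and corrects no error. The validity argument stands, and it limits the weight of the point. It does not remove the point: the protocol itself names the unadjusted test, so the choice is made here and is not simply left to the SAP, and the covariates are already being collected.

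A reader might also infer more than the text supports:
- *That the fallback loses power or inflates type I error.* The simulations show a loss of about 0.1 point under normality at 400/200, a gain of 4 to 5 points under skew or heavy tails, and type I error close to 0.01.
- *That a working vaccine would almost surely trigger the switch.* That needs pooled arms, which the protocol does not state, and a ratio near 10, where 9.5 plans for 1.35 to 1.50.
- *That the ratio is dropped once Mann-Whitney is used.* Section 9.3.2 specifies geometric means and limits and does not say they are withdrawn. It leaves open what accompanies the rank test.
- *That 9.3.2 ties the switch to Kolmogorov-Smirnov.* The link is inferred from the general sentence in 9.3.1. The fallback itself is written in advance.
- *That sections 1.1 and 4.1 omit sex.* Each includes it in one place and omits it in another.

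**Conclusion.** The point holds as a matter of efficiency and pre-specification. It does not make the primary test invalid or the trial underpowered. At one-sided 0.01, leaving out baseline costs about 3 to 14 power points with 340/170 evaluable and about 3 to 9 points at 400/200, for an assumed rho of 0.3 to 0.7, CV 1.2 and ratio 1.35. The size depends on rho, which may differ between vaccinated and unvaccinated participants; the direction holds for any non-zero rho. On the two-sided basis that reproduces the table there is no spare power at 347/173.5 (80.0%), and 340/170 gives Φ(3.383 − 2.576) = 79%, so adjustment would matter more there.

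The fallback is a separate and smaller fault. The primary test becomes data-dependent under a rule with no level, and no estimate matching the ratio in 9.1 is named for the rank test. With several hundred participants, a comparison of log means does not need exact normality, so the switch buys little. The contradiction over sex as a stratum has to be settled because it determines the adjustment set.

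**What to change.** 1. In 9.3.2, make the primary analysis a linear model of log Day 14 titre on arm, log baseline titre and the randomisation factors (as main effects), with heteroscedasticity-robust standard errors.
2. Report the adjusted geometric mean ratio with its one-sided bound, regardless of any normality test.
3. Keep the unadjusted t-test and Mann-Whitney as sensitivity analyses, and remove the conditional switch.
4. Use the same model in 9.3.3 for the Day 28 and neutralisation endpoints.
5. State one strata list in 1.1, 4.1 and 6.3, and adjust for the factors actually used in the randomisation list.

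The cost is wording in the protocol and SAP. Baseline titre, centre, age and sex are already recorded. The change should be dated before the Day 14 results are available.

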### **9.3.3. Secondary endpoint(s) analysis**

Secondary immunogenicity endpoints (serological response and neutralizing antibodies at each time point) between the two arms will be tested by one-tailed t-test assuming symmetric distribution of lognormal transformation. Geometric means will be calculated as the mean of the assay results after making the logarithm transformation and then exponentiating the mean to express results on the original scale. One-sided 95% CIs will be obtained by taking natural log transforms of concentrations/titers, calculating the 95% CI with reference to the t-distribution, and then exponentiating the confidence limits. In other case, Mann-Whitney-Wilcoxon test will be used.

For secondary efficacy objectives, the absolute and relative frequencies of individuals with molecularly confirmed COVID-19 and SIC will be compared through the two-tailed chi-square test and alpha error equal to 0.05.

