| 
Primary immunogenicity endpoint:
 
 
Serological response to vaccination (antibodies against SARS-CoV-2 spike protein) as measured by immunoassay, 14 days after vaccine dose (Group 1) or randomization (Group 2) .
 
 
Secondary immunogenicity endpoint:
 
 
Serological response to vaccination (antibodies against SARS-CoV-2 spike protein) as measured by immunoassay, 28 days after vaccine dose (Group 1) or randomization (Group 2) .
 
SARS-CoV-2 neutralization as measured by virus neutralization assay, 14 and 28 days after vaccine dose (Group 1) or randomization(Group 2) .
 
Serological response to vaccination (antibodies against SARS-CoV-2 spike protein) as measured by immunoassay at 3, 6 and 12months after randomization.
 
Neutralizing antibody titers at 3, 6 and 12 months after randomization.
 
 
Secondary efficacy endpoints:
 
 
The number of participants with molecularly confirmed COVID-19.
 
Presence and severity of COVID-19 signs and symptoms as measured by Symptoms of Infection with Coronavirus-19 (SIC).
 
 
Primary safety endpoints:
 
 
Solicited local and systemic adverse events (AEs) for a period of 7 days after vaccination.
 
Unsolicited local and systemic adverse events (AEs) for a period of 28 days after vaccination
 
Serious adverse events (SAEs) throughout the study (from randomization until end of the study).
 
Medically-attended adverse events (MAAEs) from the day of vaccination until 6 months after the last vaccination.
 
Abnormal laboratory parameters at 1 month visit after COMIRNATY vaccination.
 
 |                                                                                                                                         |

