#### **Trial Duration:**

First analysis (completed 14 day) will be available about 5 weeks after first patient inclusion.

Each patient will be followed for 1 year.

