## **4. Study Design**

### **4.1. Overall Design**

This is a randomized, non-blinded, controlled, adaptive, multicenter, Phase II study in subjects aged more than 18 years and in good health or stable clinical situation that have received a previous single dose of VAXZEVRIA.

This is a phase 2 adaptive trial developed for evaluating the immunogenicity of a dose of COMIRNATY after a previous single dose with VAXZEVRIA. A stratification will be made for the following factors: site of vaccination, sex and age. This protocol allows to test the immunogenicity and safety of a heterologous vaccination strategy after a single dose of VAXZEVRIA.

Subjects will be randomized to immediately receive or not dose of COMIRNATY in a proportion of 2:1.

If primary analysis at 14 days confirms the starting hypothesis, subjects randomized to no vaccination will be considered for administration of one dose of COMINARTY at day 28th according to Public Health Department of the Ministry of Health recommendations on heterologous vaccination. If vaccinated, subjects will be followed at the time points defined in the flowchart.

In case the primary analysis does not confirm the starting hypothesis, subject will be followed without administration of COMINARTY.

In case Public Health Department gave instructions to give the second dose of VAXZEVRIA to those subjects having received the first dose, subject will be followed as indicated in flowchart of Group 2.

Other heterologous vaccination strategies could be incorporated if deemed necessary for public health reasons. This could include the use of different boost strategies including those already marketed vaccines for comparative assessment of their safety and efficacy on SARS-CoV-2 and its variants.

The different intervention arms planned (and its corresponding control arm) can be carried-out in different trial sites, thus not all trial sites must participate in all arms.

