## **7. Discontinuation of Study Intervention and Participant Discontinuation/Withdrawal**

### **7.1. Discontinuation of Study Intervention**

This is not applicable. Intervention is a unique dose of COMIRNATY in the randomization visit.

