| DPS2                     | 
 
For participants who discontinue study intervention and/or receive rescue therapy, post-discontinuation or post-rescue observations will not be included.
 
 |

Full analysis set and DPS1 are used to estimate the primary endpoints and the secondary endpoints for secondary core objective.

Full analysis set and DPS2 are used to for sensitivity analyses.

Safety analysis set and DPS1 are used to present safety data.

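### If controls are boosted at Day 28, the one-tailed between-arm antibody tests at 6 and 12 months no longer compare boost with no boost, and crossed-over controls have no 3-month sample

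*Protocol*

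**What the plan says.** **Tests.** Section 9.3.3 fixes the method: "Secondary immunogenicity endpoints (serological response and neutralizing antibodies at each time point) between the two arms will be tested by one-tailed t-test". The intervals are one-sided 95%. The synopsis sets the late time points for binding antibodies ("as measured by immunoassay at 3, 6 and 12months after randomization") and for neutralising antibodies ("Neutralizing antibody titers at 3, 6 and 12 months after randomization"). Table 3.1 counts the same months from the boost dose instead.

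**Crossover.** Under section 4.1, if the Day 14 analysis confirms the hypothesis, "subjects randomized to no vaccination will be considered for administration of one dose of COMINARTY at day 28th", subject to public health recommendations. The synopsis and section 6.1.2 say the same. The synopsis and section 4.1 also foresee a second VAXZEVRIA dose if the authorities instruct it.

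**Data sets.** In section 9.2 the full analysis set groups participants as randomised. DPS1, which keeps every observation, serves the primary and secondary endpoints. DPS2 is for sensitivity analyses: "For participants who discontinue study intervention and/or receive rescue therapy, post-discontinuation or post-rescue observations will not be included". Section 7.1 says of discontinuation: "This is not applicable. Intervention is a unique dose of COMIRNATY in the randomization visit". Rescue therapy is not defined anywhere in the protocol.

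**Schedule.** In the Group 2 crossover flowchart (section 1.2), Visit 4 carries the boost and Visit 5 is at Day 56. In Group 1, Visit 5 is at Day 90. Controls who do not cross over follow the Group 1 visits.

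**The concern.** The trial hypothesis in section 3 is that boosting gives a better response than not boosting, and section 9.1 sets the one-sided alternative accordingly. That contrast exists only while Group 2 remains unboosted. Crossover is triggered by success of the primary analysis, so the difficulty arises in the very scenario the trial is powered for.

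Nothing in the protocol limits the between-arm tests to samples taken before crossover, times Group 2 from its own boost, or makes the late tests depend on whether crossover occurs. A non-significant 6- or 12-month result could then be read as loss of benefit from the boost when both arms had been boosted. DPS2 would not warn the reader, because a crossover dose is neither discontinuation nor defined rescue.

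**Working it through.** **1. The plan's own figure.** Section 9.5 gives 173.506 controls and 347.012 COMIRNATY participants for a coefficient of variation (CV) of 1.2 and a ratio of 1.35.
- SD on the log scale = √ln(1 + 1.2²) = 0.944.
- n(control) = 1.5 × [SD × (z_α + z_0.80) / ln 1.35]².
- With two-sided α = 0.01 this gives 173.506, and all 12 table rows match to three decimals. With the stated one-sided 0.01 it gives 149.1. That mismatch is a separate matter; the match confirms the log-scale model used below.
- 520.518 × 1.15 = 598.6, about the planned 600.

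This calculation concerns Day 14, before any crossover.

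**2. What the crossover schedule can supply** (boost on Day 28)

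| Visit | Group 1, days since boost | Crossed-over Group 2, days since boost |
|---|---|---|
| 5 | 90 | 56 − 28 = 28 |
| 6 | 180 | 180 − 28 = 152 |
| 7 | 360 | 360 − 28 = 332 |

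Group 1's Visit 5 window is Day 80 to 100. Crossed-over Group 2's is Day 46 to 66 in the flowchart (56±10) or Day 53 to 59 in section 8 (56±3). On either version they do not overlap, so there is no 3-month sample after randomisation. Counting from the boost, as Table 3.1 does, gives about Days 118, 208 and 388 for Group 2. Each lies outside the scheduled windows (Visit 6: Day 170 to 190; Visit 7: Day 346 to 374 at the widest).

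**3. Effect on the one-tailed test.** The inputs from section 9.5 are a ratio of 1.35, CV 1.2 and 400 v 200, all taken as evaluable. Two further assumptions are mine: a fraction f of controls is boosted, and boosted controls have the same late titres as Group 1.
- Expected log difference d = (1 − f) × ln 1.35.
- Group 2 variance = SD² + f(1 − f)(ln 1.35)².
- SE = √(SD²/400 + Group 2 variance/200).
- Power = Φ(d/SE − z_α).

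At f = 0, d = 0.300 and SE = 0.0818, so power at one-sided 0.05 is Φ(3.67 − 1.645) = 97.9%. At f = 0.5, d = 0.150 and SE = 0.0825, so it is Φ(1.82 − 1.645) = 56.9%.

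| f | As-randomised ratio | Power, one-sided 0.05 | Power, one-sided 0.01 |
|---|---|---|---|
| 0 | 1.35 | 97.9% | 91.0% |
| 0.25 | 1.25 | 86.2% | 65.9% |
| 0.5 | 1.16 | 56.9% | 30.6% |
| 0.75 | 1.08 | 23.2% | 7.9% |
| 1 | 1.00 | 5.0% | 1.0% |

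The 0.05 column matches the one-sided 95% intervals of section 9.3.3; the 0.01 column uses the level in section 9.5.

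**4. The opposite direction.** If all controls cross over and, having been boosted later, have titres 10% higher than Group 1 (an assumption), the ratio is 1/1.10 = 0.91. The one-tailed test at 0.05 then rejects in under 0.3% of trials.

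**The case against.** The strongest reply is that the problem is conditional and secondary. Crossover needs a positive primary analysis and public health agreement. The Day 7 and Day 14 analyses precede it, and the Day 28 sample is clean if drawn before the dose. All of that stands.

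It can also be said that only the primary objective names no dosing as comparator, and that immediate versus deferred boosting is a legitimate randomised contrast. That is fair, and it is a reason to report the late data under that label. It does not justify a one-sided test whose alternative is boosted above unboosted.

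Finally, section 9 is a summary and the SAP, not at hand, may handle crossover. But the protocol itself fixes the test, its direction, the time points and the data sets, and describes the SAP as giving more detail on these same analyses.

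Three stronger readings are tempting and are not supported:
- **No Day 42 sample and a wrong baseline for controls.** The synopsis plans "Change in immune response from baseline (randomization visit) to 14 and 28 days after COMIRNATY vaccination in the immediate and control groups". Timed from a Day 28 boost, the 14-day value would fall near Day 42, where no visit exists. But the synopsis endpoints time Group 2 from randomisation at 14 and 28 days; on that reading both samples exist and the randomisation visit is the right baseline. The wording needs clarifying; an error is not shown.
- **The analysis comes too late for the first controls' Day 28 visit.** The synopsis says "First analysis (completed 14 day) will be available about 5 weeks after first patient inclusion". Five weeks is 35 days and the visit window closes at Day 31. However, the figure is approximate, and if inclusion is counted from consent, up to 7 days of screening places it between study Days 28 and 35. No conflict is established.
- **A definite reversal of the ratio.** An antibody half-life of 40 to 100 days would give 2^(−28/40) = 0.62 to 2^(−28/100) = 0.82. This needs full crossover, equal peaks, constant decay and a half-life that the protocol does not give.

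**Conclusion.** The point holds, conditionally on crossover. If Group 2 is boosted, the fixed 6- and 12-month one-tailed tests no longer answer whether boosting beats not boosting, and crossed-over controls contribute no 3-month sample. Power falls with the crossed fraction, from 97.9% to 56.9% at half and 5.0% at full crossover at one-sided 0.05.

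These figures rest on the Day 14 ratio of 1.35 holding at late time points, CV 1.2, full follow-up, and crossed controls equal to Group 1. With another true ratio R, the as-randomised ratio would be R^(1 − f): a larger R keeps more power under partial crossover, but the estimate is still diluted and still reaches 1.00 at full crossover. It would therefore be wrong to infer that the late tests have almost no power in general. If no crossover occurs, and no second VAXZEVRIA dose is given, they remain valid.

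DPS2 as written offers no sensitivity analysis for crossover.

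**What to change.** 1. In section 9.3.3, make the rule conditional. If Group 2 receives any further SARS-CoV-2 vaccine dose, limit the one-tailed boost versus no-boost tests to samples up to and including the Day 28 sample, and state that this sample is the one drawn before that dose. If no crossover occurs, keep the planned late tests.
2. After crossover, report geometric means and ratios with two-sided 95% intervals, labelled immediate versus delayed boosting, and also by days since each participant's actual boost. Use the Day 28 pre-boost sample as baseline for any Group 2 post-boost change.
3. Redefine DPS2 to exclude observations after a non-randomised SARS-CoV-2 vaccine dose. Under full crossover this leaves no late Group 2 data, and the text should say so. Under partial crossover the remaining controls are a selected group, so the result is supportive only.
4. Clarify in the synopsis whether the control-group changes at 14 and 28 days run from randomisation or from the Day 28 boost. Reconcile the origin of the 3-, 6- and 12-month time points between the synopsis and Table 3.1, and the Visit 5 window between the flowchart and section 8.

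The cost is protocol and SAP wording, plus the loss of late between-arm p-values if crossover occurs. No sample size change is needed.
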